## Abstract

Atopic dermatitis (AD) is a chronic inflammatory skin disease with persistent itching, which impairs quality of life (QoL). Although various conventional treatments for AD exist, patients with AD often seek complementary and alternative therapies when conventional therapy has failed to relieve their AD symptoms or has had adverse effects. Acupuncture treatment may relieve AD symptoms, but controlled trials are needed to confirm this. Following our pilot study, which found that acupuncture treatment improves AD symptoms in mild-to-moderate AD patients, we will assess the effect of acupuncture treatment for symptom relief of AD using a trial with a complemented protocol. This is a two-arm, randomized, participant- and assessor-blinded, sham-controlled trial. A total of 36 mild-to-moderate AD patients will be randomly assigned in a 1:1 ratio to receive eight sessions twice weekly of either verum acupuncture (VA) or nonpenetrating sham acupuncture (SA) over four weeks. The primary outcome measured will be the change in the total Scoring Atopic Dermatitis (SCORAD) score. Secondary outcomes will be (1) changes in AD symptoms, QoL, dyspepsia symptoms, and electroencephalography (EEG) between baseline and week 4 and (2) changes in AD symptoms and QoL at baseline and at weeks 2, 4, and 8. This study will assess acupuncture treatment for the alleviation of AD symptoms in patients with mild-to-moderate AD. This clinical trial gas been registered in Korean Clinical Trial Registry (registration number: KCT0002796; date of registration: April 13, 2018).

## 1. Introduction

Atopic dermatitis (AD) is a chronic inflammatory skin disease characterized by intense itching, skin dryness, erythema, exudate, crust, and lichenification [1]. Globally, AD is a common health problem, and its incidence rate has increased 2-3 times in recent years in industrialized countries. Approximately, 20% of children and 3% of adults are suffering from AD [2, 3].

Initial treatments for AD are emollients, topical corticosteroids, and topical calcineurin inhibitors [4, 5]. Depending on severity, antihistamines, systemic corticosteroid, immunosuppressant, antibiotics, allergen-specific immunotherapy, or phototherapy may be used [6–8]. Complementary and alternative medicine treatments are used in patients with AD, especially when there is no response to conventional therapies or side effects occurring [9–11].

AD has been effectively treated with acupuncture, which has been shown to lack side effects when used with conventional therapies [12–16]. In animal models, acupuncture treatment resulted in decreased skin overgrowth and pruritus and improved biomarkers [5, 17]. To our knowledge, randomized controlled studies of the effectiveness of acupuncture-only treatment for AD are lacking [18], with the exception of our pilot study [19].

In this pilot study [19], a verum acupuncture (VA) treatment group showed significant alleviation of AD symptoms relative to the sham acupuncture (SA) group, including pruritus. Also, we found a positive relationship between the severity of AD symptoms and gastrointestinal (GI) symptoms such as epigastric tenderness and dyspepsia. Several studies show that GI and AD symptoms are related to unbalance of autonomic nerve system with sympathetic hyperactivity and parasympathetic dysfunction [20, 21]. Acupuncture treatment is known to affect autonomic nerve system [22]. Also, the relationship between AD and the central nervous system (CNS) has been well studied. Stress aggravates and sustains the itch-scratch cycle of AD by affecting the CNS [23]. Acupuncture treatment of AD patients may reduce brain activity of the insula, putamen, premotor and prefrontal cortical areas, which is induced by itching [24]. These findings can support the hypothesis of a “gut-brain-skin axis” suggesting a relationship between the GI tract, brain, and skin [25].

Taken together, this recent evidence suggests the need for a randomized controlled trial assessing the efficacy of acupuncture in reducing the symptoms of AD. This study protocol describes the first such study. We designed a two-arm, randomized, participant- and assessor-blind, sham-controlled trial based on our pilot study and the above recent studies. The trial aims to assess the effect of twice-weekly acupuncture treatment on the symptoms of mild-to-moderate AD in adults, including changes in quality of life (QoL), GI symptoms, and EEG.

## 2. Methods

### 2.1. Objectives

The main study objective is to determine whether or not twice-weekly acupuncture treatment improves symptoms and quality of life (QoL) in adults with mild-to-moderate AD.

Other objectives are (1) to investigate the relationship between severity of AD symptoms and GI symptoms and (2) to determine the effect of acupuncture on the CNS of AD patients using EEG.

### 2.2. Trial Design and Setting

This is a randomized, participant- and outcome assessor-blind, sham-controlled trial with a parallel group design. It will be conducted at the Kyung Hee University Korean Medicine Hospital. The flow chart of the study is presented in Figure 1.

### 2.3. Eligibility Criteria

Inclusion/exclusion criteria are as follows.

#### 2.3.1. Inclusion Criteria

(A) 19 to 65-year-old men and women able to read and write the Korean language

(B) AD diagnosed according to the Hanifin and Rajka criteria [26]

(C) Scores from 30 to 80 points on a 100 mm Visual Analog Scale (VAS) for pruritus (0, no symptom at all; 10, worst symptom ever) [27]

(D) Scores from 10 to 40 points on the objective Scoring Atopic Dermatitis (SCORAD) scale [28]

(E) Abstinence from prescribed medications for AD for the preceding month

(F) Agreement with a study protocol and willingness to sign written informed consent

(G) No participation in other clinical studies for the preceding month

#### 2.3.2. Exclusion Criteria

(A) Severely fluctuating AD symptoms

(B) Treatments (e.g., oral steroids) that may affect the symptoms of AD or that the study KMD deems inappropriate

(C) Secondary infection of AD lesions

(D) Severe mental problems

(E) Pregnancy, breastfeeding, or plans to have a baby during the study period

(F) Medical history that the study KMD considers to be inadequate

### 2.4. Recruitment of Participants

Based on our pilot study [19], we aim to recruit 36 mild-to-moderate AD patients using posters on noticeboards at the Kyung Hee Medical Center, nearby schools, and local community centers.

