#### 2.7.2. Verum Acupuncture (VA) Group

Participants in the VA group will receive eight acupuncture treatments twice a week for a total of four weeks. All VA group patients will receive acupuncture needling at six fixed acupoints. Up to 10 additional acupoints will be used, depending on each participant's daily general conditions. The six fixed acupoints are LI11, ST36, and PC6 bilaterally. Additional acupoints include ST43, GB41, LI2, TE3, SI3, TE6, SI2, BL66, LR3, SP3, ST43, and GB41 for gastric stuffiness or dyspepsia; LI2 and GB41 for tenderness around ST25, diarrhea, or constipation; TE3 and SI3 for fullness in the chest and hypochondrium; TE3 and TE6 for lower abdominal pain and tenderness on CV17; SI3 and GB41 for lower abdominal pain and dry skin; SI2 and BL66 for lower abdominal pain and heat in the upper body and cold in the lower body; and LR3 and SP3 for pain in the hypogastric region with darkness of the sublingual collateral vessels. Disposable sterile stainless needles (0.25 x 40 mm; Dongbang Acupuncture Inc., Bundang, Seongnam, Korea) will be used. Acupuncture needles will be inserted to depths of 5 to 30 mm, depending on the acupoint, and will remain in place for 15 minutes.

After removal of acupuncture needles, three acupoints will be treated with IA using 1.5 mm press tack needles (Haeng Lim Seo Won Medical Co., Korea). These are bilateral LI11 and auricular-Shenmen contralaterally to the side with more severe symptoms. Participants will be instructed by the study KMD to press LI11 for more than three minutes when they experience severe itching.

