#### 2.7.3. Sham Acupuncture (SA) Group

Participants in the SA group will receive sham acupuncture treatment eight times twice a week for four weeks. Unlike the VA group, SA group patients will receive sham acupuncture treatment at only six fixed control points. These bilateral acupoints are as follows: 1 to 2 cm proximal and 1 cm medial to LI7, 1 cm proximal and 1 cm medial to LI11, and 1 cm proximal and 1 cm lateral to ST36. To maintain participant blinding, a nonpenetrating sham device (Park sham acupuncture needles, AcuPrime Co., Ltd., Exeter, UK) will be used and left in place for 15 minutes.

After removal of sham acupuncture needles, the IA procedure used in the VA group will be replaced with application of needle-free, stainless steel rings that do not penetrate the skin. These will be attached to three control points: 1 cm proximal and 1 cm medial to LI11 bilaterally and finger point in the ear contra-laterally to the side with more severe symptoms. Unlike the VA group, SA group patients will not be instructed to press the control point.

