#### 2.9.1. Scoring Atopic Dermatitis (SCORAD)

SCORAD was developed in 1993 by the European Task Force on Atopic Dermatitis as a useful scoring system that assesses the severity of AD by its extent, intensity, and subjective symptoms [28, 30, 31]. The extent component of SCORAD is assessed using the rule of nines for AD lesions. The intensity component of SCORAD is divided into erythema, edema and papules, oozing and crust, excoriation, lichenification, and dryness. Subjective symptom measures are the degrees of pruritus and sleep disturbance assessed on the VAS.

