	(2c) Depth of insertion, based on a specified unit of measurement or on a particular tissue level MA: From 5 to 30 mm, perpendicular to skin surface IA: 1.5 mm, perpendicular to skin surface (2d) Response sought (e.g., de qi or muscle twitch response) MA: “de qi” sensation IA: None (2e) Needle stimulation (e.g., manual, electrical) MA: Manual stimulation, needle rotation with thumb and index fingers for the first 10-15 seconds IA: Participants will be educated to press PTNS at LI11 for more than 3 minutes when they feel severe itching (2f) Needle retention time MA: 15 minutes IA: 1-2 days until PTN falls off (2g) Needle type (diameter, length, and manufacturer or material) MA: A sterilized stainless steel needle (0.25 x 40 mm, Dongbang Acupuncture Inc., Bundang, Seongnam, Korea) IA: A hypoallergic PTN (1.5 mm, 10 x 10 mm adhesive tape, Haeng Lim Seo Won Medical Co., Korea)

(3) Treatment Regimen	(3a) Number of treatment sessions
	(i) 8 sessions
	(3b) Frequency and duration of treatment sessions
	(i) Twice a week for 4 weeks, 15 minutes for each session

(4) Other Components of Treatment	(4a) Details of other interventions administered to the acupuncture group (e.g. moxibustion, cupping, herbs, exercises, lifestyle advice)
	(i) Lifestyle advice will be given to all participants
	(ii) Any other interventions will be prohibited during study period
	(4b) Settings and context of treatment, including instructions to practitioner and information and explanations to patients
	(i) Participants will be informed about acupuncture treatment in the study as follows: “In this study, you will be randomly allocated to VA group or SA group. Acupoints will be selected based on traditional Korean medicine textbook and AD-related reports. Also, additional acupoints can be used according to individual conditions, if needed.”

(5) Practitioner Background	(5) Description of participating acupuncturists (qualification or professional affiliation, years in acupuncture practice, other relevant experience)
	(i) KMD who has clinical experience in Korean Medicine dermatology more than 2 years. The practitioner KMD will have undergone more than 10 hours of training and simulation workshop to ensure that he is able to provide identical acupuncture treatment in accordance with a predefined protocol.

(6) Control and Comparator Interventions	(6a) Rationale for the control or comparator in the context of the research question, with sources that justify this choice

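### Eligibility does not exclude acupuncture-trained people or the investigators' own staff and students, who might infer their arm from where the patches sit

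*Protocol article*

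**What the plan says.** Section 2.2 sets the trial in a Korean medicine hospital: "It will be conducted at the Kyung Hee University Korean Medicine Hospital". Section 2.4 recruits 36 patients through "posters on noticeboards at the Kyung Hee Medical Center, nearby schools, and local community centers".

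The inclusion criteria (2.3.1, A to G) open with "19 to 65-year-old men and women able to read and write the Korean language" and go on to diagnosis, itch, objective SCORAD, medication, consent and other trials. In the exclusion criteria (2.3.2, A to F), the broadest discretionary item is "Medical history that the study KMD considers to be inadequate". That item concerns medical history. No item mentions acupuncture training, or working or studying under the investigators.

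The patches applied after each session go to different places in the two arms:

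- Verum (2.7.2): "These are bilateral LI11 and auricular-Shenmen contralaterally to the side with more severe symptoms".
- Sham (2.7.3): "1 cm proximal and 1 cm medial to LI11 bilaterally and finger point in the ear contra-laterally to the side with more severe symptoms".

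Table 1, item (2f), has the verum press tacks staying on for 1-2 days until they fall off. The screen described in 2.6 is used during treatment. Table 1, item (4b), gives the wording used with participants: "Acupoints will be selected based on traditional Korean medicine textbook and AD-related reports", followed by a statement that further points may be added for individual conditions.

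The primary outcome is the change in total SCORAD to week 4. Section 2.9.1 describes its subjective part: "Subjective symptom measures are the degrees of pruritus and sleep disturbance assessed on the VAS".

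**The concern.** The trial is described as participant-blinded. The measures that protect the blind deal with seeing the procedure (the screen), with whether a needle penetrates (the Park device in both arms), and with the look of the patch (a same-sized ring without a needle). None of them hides where the patch is.

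For most patients location carries no information. For someone who has learned LI11 and the ear points it might, and the participant can examine the patches at home. The setting and the recruitment sites make it plausible that a few such people would volunteer, and the eligibility criteria do not keep them out. Staff or students of the investigators' units may also feel pressure to report a good result, whether or not they know their arm.

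Itch and sleep loss within SCORAD, and the patient-reported scales such as POEM and DLQI, would carry any expectancy effect straight into the comparison of the arms.

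**Working it through.** **1. The plan's own figure.** Section 2.10 gives changes of 13.0 ± 9.9 (verum) and 4.6 ± 5.0 (sham).

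- Difference: 13.0 − 4.6 = 8.4 points.
- Pooled SD: √((9.9² + 5.0²)/2) = √61.505 = 7.84.
- d = 8.4/7.84 = 1.07, stated as 1.1.
- With 15 per arm (28 df), the critical t is 2.05, the noncentrality is 2.93 (3.01 with d = 1.1) and power is 81% (83%).
- 15 × 1.2 = 18 per arm.

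The stated 18 reproduces, and an added exclusion does not change it.

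**2. How far apart the sites are.** The sham elbow site is 1 cm proximal and 1 cm medial to LI11: √(1² + 1²) = 1.4 cm. The verum tape is 10 × 10 mm (Table 1, item 2g). The ear sites are two different named points.

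**3. Illustrative effect on the primary test.** The documents give neither input, so both are assumed:

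- s = share of each arm that infers its allocation (10%, 20%, 30%).
- k = points by which each such person shifts self-rated itch plus sleep, downwards in verum and upwards in sham (2 or 4).

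Bias in the verum-minus-sham difference = 2 × s × k. With no true effect and 18 per arm (34 df), the noncentrality is bias/7.84 × √(18/2). The two-sided rejection rate at nominal 5% comes from the noncentral t.

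| s (of 36) | k | Bias | Share of 8.4 | Type I error |
|---|---|---|---|---|
| 10% (about 4) | 2 | 0.4 | 5% | 0.053 |
| 10% | 4 | 0.8 | 10% | 0.060 |
| 20% (about 7) | 2 | 0.8 | 10% | 0.060 |
| 20% | 4 | 1.6 | 19% | 0.091 |
| 30% (about 11) | 2 | 1.2 | 14% | 0.073 |
| 30% | 4 | 2.4 | 29% | 0.145 |

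**4. Sensitivity to the SD.** Giving both arms the sham SD of 5.0 raises the range over the same grid to 0.056-0.288. That ignores the 9.9 which section 2.10 gives for verum, so it is an extreme case and I do not rely on it.

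**The case against.** The strongest reply is that this is an absent safeguard and not an error. Section 2.4 contradicts nothing, using different sites in the two arms is a deliberate choice explained in the Discussion, and rules for dependent staff and students may stand in the full protocol or the ethics file. That is fair, and it is why the point is graded as an improvement. Even so, the article sets out its criteria item by item, and no item covers this.

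A reader might infer that recruitment lets in people who can read their arm, or that the posters are themselves at fault. The documents support neither:

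- Section 2.4 names a medical centre, schools and community centres. It describes no staff or student areas and does not say what kind of schools they are.
- An offset of 1.4 cm under 10 mm tape may be hard to judge, the wearer cannot see the ear patch directly, and the sham ear site is itself a named point.
- Because participants are told that extra points may be used, an unfamiliar site does not by itself signal sham.

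The protocol also has safeguards. Table 1, item (6b), says the sham patch was designed and validated for blinding. Section 2.9.9 tests credibility repeatedly and asks participants, at the eighth treatment visit, which group they think they were in and why. These count, but only in part: a look-alike ring does not disguise its position, and the guess question detects unblinding once treatment is over without preventing it.

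Finally, only verum participants are told to press LI11 when itching is severe (2.7.2 and 2.7.3). That difference needs no training to matter and reaches every participant, so it may well be the larger cue. It is a separate issue, and it does not remove this one.

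**Conclusion.** The gap in eligibility is real. Neither list excludes acupuncture-trained people or dependent staff and students, the patch sites differ by arm, the verum patches outlast the screened session, and part of the primary outcome is self-rated. A knowledgeable participant may be able to infer the arm. The documents do not show that any will.

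The likely size is modest. It is tempting to say that a handful of such people in a trial of 36 would be enough to matter, but the figures do not bear that out: about 4 of 36 moves the type I error only to 0.053-0.060. Reaching 0.145 takes about 11 of 36, each shifting by 4 points, which means an 8-point gap between those participants in the two arms, nearly the whole planned 8.4. All of these figures rest on assumed shares and shifts, a common SD of 7.84, 18 analysed per arm and no true effect.

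**What to change.** Add one exclusion to section 2.3.2 for people trained or in training in acupuncture or Korean medicine, and for staff or students of the hospital, the research centre or the investigators' units. Check it with one screening question.

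The cost is a short amendment and a slightly smaller recruitment pool. Sample size, visits and procedures stay the same, and poster placement need not change. The fix does not touch the press instruction given only to the verum arm, which has to be considered separately.

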### 2.5. Randomization and Allocation Concealment

Participants who meet the inclusion criteria and have signed the written informed consent will be randomly assigned to either the VA or the SA group in a 1:1 ratio. An independent statistician will generate a random number table using SAS 9.2 (PROC PLAN, SAS Institute Inc., Cary, NC, USA) and send it to the administrative staff at the Acupuncture and Meridian Science Research Center (AMSRC) at Kyung Hee University. The administrative staff, who are also independent of our research team, will put each random number in a sealed, sequentially numbered, opaque envelope. Once a participant passes screening, the investigator will call the AMSRC staff, who will immediately send the investigator a document containing that participant's unique random number and group allocation, which will be kept in the trial master file.

### 2.6. Blinding and Code Breaking

Participants and outcome assessors will be kept ignorant of treatment group allocations. It is not possible to blind the acupuncturist, so the KMD who applies the acupuncture treatment will not participate in assessment of trial outcomes or in collecting and analyzing the data. During acupuncture treatment, all participants in both groups will be shielded by a screen so that they cannot see the procedures. All participants in both groups will be treated with a Park sham device to ensure ignorance of whether the acupuncture needles penetrate the skin or not. If severe side effects occur or immediate acupuncture cessation is required, the blinding code will be broken.

### 2.7. Interventions

#### 2.7.1. Acupuncture Treatment

Acupuncture treatment details are presented in Table 1 and are based on the revised Standards for Reporting Interventions in Clinical Trials of Acupuncture (STRICTA) 2010 checklist. Manual acupuncture (MA) and intradermal acupuncture (IA) will be performed for all participants in the VA group. All acupuncture treatments will be administered by one KMD with more than two years of clinical experience in Korean Medicine dermatology. This KMD will have undergone more than 10 hours of training and simulation to ensure that he is able to provide identical acupuncture treatment in accordance with the predefined protocol.

#### 2.7.2. Verum Acupuncture (VA) Group

Participants in the VA group will receive eight acupuncture treatments twice a week for a total of four weeks. All VA group patients will receive acupuncture needling at six fixed acupoints. Up to 10 additional acupoints will be used, depending on each participant's daily general conditions. The six fixed acupoints are LI11, ST36, and PC6 bilaterally. Additional acupoints include ST43, GB41, LI2, TE3, SI3, TE6, SI2, BL66, LR3, SP3, ST43, and GB41 for gastric stuffiness or dyspepsia; LI2 and GB41 for tenderness around ST25, diarrhea, or constipation; TE3 and SI3 for fullness in the chest and hypochondrium; TE3 and TE6 for lower abdominal pain and tenderness on CV17; SI3 and GB41 for lower abdominal pain and dry skin; SI2 and BL66 for lower abdominal pain and heat in the upper body and cold in the lower body; and LR3 and SP3 for pain in the hypogastric region with darkness of the sublingual collateral vessels. Disposable sterile stainless needles (0.25 x 40 mm; Dongbang Acupuncture Inc., Bundang, Seongnam, Korea) will be used. Acupuncture needles will be inserted to depths of 5 to 30 mm, depending on the acupoint, and will remain in place for 15 minutes.

After removal of acupuncture needles, three acupoints will be treated with IA using 1.5 mm press tack needles (Haeng Lim Seo Won Medical Co., Korea). These are bilateral LI11 and auricular-Shenmen contralaterally to the side with more severe symptoms. Participants will be instructed by the study KMD to press LI11 for more than three minutes when they experience severe itching.

